### Study timeline

The first clinic visit starts with written informed consent, and when participants are eligible, the baseline assessment will be performed. The baseline assessment consists of questionnaires (frailty status, risk of sarcopenia, self-reported mobility limitations, QoL and healthcare costs) and measurements (physical function, muscle strength and body composition). See below ‘primary and secondary outcomes’ and ‘other measures’ for details on these assessments. An accelerometer will be attached to measure physical activity for 7 subsequent days.

After the baseline assessment, participants will be randomised to one of the three study groups done by the nutritionists and they will inform the participants in which group they are allocated to. Participants randomised to one of the two intervention groups will be invited for a consultation meeting at the clinic to receive their personalise d dietary advice, and personalised advice on optimising the timing of protein intake in close proximity of usual physical activity (intervention group 2 only). This will take place within 2 weeks after the baseline assessment since the personalised advice needs to be composed by the nutritionist. The baseline assessment is considered the start of the study period for participants of the control group, while the consultation meeting is considered the start of the study period for participants of the intervention groups.

One week prior to the 3-month follow-up visit, dietary intake will be assessed again by means of a combination of three food diaries and three 24-hour dietary recalls. The 3-month follow-up visit will take place at the clinic and includes measurement of BW, assessment of self-reported mobility limitations, risk of sarcopenia, QoL, healthcare costs and the accelerometer will be attached to measure physical activity for 7 subsequent days.

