One week prior to the 6-month follow-up visit (final measurement), dietary intake will again be assessed by means of a combination of three food diaries and three 24-hour dietary recalls, which allows us to determine compliance to the dietary advice. The 6-month follow-up visit at the clinic includes all measurements performed during the baseline visit and the accelerometer is attached again to measure physical activity for the next 7 days. Finally, among participants of the intervention groups only, several questions regarding the appreciation and adherence of the intervention and participants’ intention to follow the dietary advice in the future will be asked in order to perform a process-evaluation. Figure 1 shows the study timeline and table 1 provides an overview of all measurements.

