Self-reported mobility limitations will be assessed by means of a questionnaire; ‘Because of your health, how much difficulty do you have walking 400 metre?’ and ‘Because of your health, how much difficulty do you have climbing 10 steps?’ Participants will respond using a 5-level Likert scale: ‘no difficulty’, ‘a little difficulty’, ‘some difficulty’, ‘a lot of difficulty’ and ‘unable to do the activity’. Mobility limitation is defined as two consecutive reports of having any difficulty walking 400 m or climbing 10 steps without resting due to a health or a physical problem.

QoL will be measured using the EuroQol 5D-5 L Questionnaire.^63^

Incident frailty will be assessed using the Fried criteria.^64^ Participants will be considered ‘frail’ when three or more components are present. Those with no components will be considered ’robust’, whereas those with one or two components will be considered ’prefrail’. The criteria include (1) self-reported unintentional weight loss (>4 kg in past 6 months), (2) self-reported exhaustion (based on two questions from the Center for Epidemiologic Studies Depression Scale on exhaustion in the past week at baseline and follow-up: ‘I felt that everything I did was an effort’ and ‘I could not get going’. Scores range from 1 ‘rarely or none of the time’ to 4 ‘always or most of the time’. A score of 3 or 4 on either question indicates exhaustion,^65^ (3) weakness (grip strength in the lowest 20% of the whole study population based on the mean of the maximum scores, adjusted for gender and BMI), (4) slow walking speed (walk time on the 4 m walk test in the slowest 20% of the whole study population, adjusted for gender and height), and (5) low physical activity (total counts per week based on the accelerometer data in the lowest 20% of physical activity for each gender). Incident frailty is considered deterioration of frailty status; that is, from robust at baseline to prefrail or frail at follow-up or from prefrail at baseline to frail at follow. Frail participants at baseline will be excluded from these analyses.

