#### Statistical analyses plan

Statistical reporting will be according to the Consolidated Standards of Reporting Trials standards.^70^ The collected data at the two study sites will be pooled together at the Amsterdam site, with a variable indicating study site. All statistical analyses on primary and secondary outcome measures will be performed by an independent statistician blinded for group allocation. Baseline characteristics will be described (percentages, means±SDs) by study group.

The primary analyses will be based on the intention-to-treat principle, that is, data from participants allocated to the intervention groups will be analysed as part of those groups, irrespectively of their level of adherence to the advice. Multiple imputation using Multivariate Imputation by Chained Equations will be used to impute missing cost and effect data. The continuous primary outcome (change in 400 m walk time) will be analysed using mixed model regression analyses with study site as random variable. We will adjust for baseline 400 m walk time as well as baseline protein intake (g/kg aBW/day) and sex (the stratification factors for randomisation). We will compare intervention effects of the respective intervention groups versus the control group. Effects will also be expressed in Cohen’s d and the corresponding 95% CIs will be calculated, which allows comparison between intervention effect estimates between different outcome measures. The secondary outcomes and other measures will be analysed using mixed model regression analogously to the primary outcome. For binary secondary outcomes, generalised estimating equation models will be used. With regard to time-to-event analyses (incident sarcopenia risk and mobility limitations) Cox proportional hazard models will be used. Time-to-event is defined as the time of the start of the study period to the date of the first occurrence of the event (3-month follow-up visit or 6-month follow-up visit). Participants who do not meet these criteria will be censored at the latest time we had information available. We will perform subgroup analyses stratified by baseline protein intake (<0.9 or 0.9–1.0 g/kg aBW/day), sex and baseline 400 m time (based on median) for the primary and secondary outcomes.

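### Cox models that use the visit date as the event time make two secondary hazard ratios depend on when each arm is seen; analyse by scheduled visit instead

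*Protocol article*

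**What the plan says.** The Statistical analyses plan section names the model: "With regard to time-to-event analyses (incident sarcopenia risk and mobility limitations) Cox proportional hazard models will be used". Event time runs from the start of each participant's study period "to the date of the first occurrence of the event (3-month follow-up visit or 6-month follow-up visit"). Of everyone else it says: "Participants who do not meet these criteria will be censored at the latest time we had information available".

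The Study timeline section and Table 1 show when these states can be observed. Of the middle visit: "The 3-month follow-up visit will take place at the clinic and includes measurement of BW, assessment of self-reported mobility limitations, risk of sarcopenia". Of the last: "The 6-month follow-up visit at the clinic includes all measurements performed during the baseline visit". There is no assessment in between. For the mobility outcome, the Secondary outcomes section adds: "Mobility limitation is defined as two consecutive reports of having any difficulty walking 400 m or climbing 10 steps". That event can therefore also be met for the first time only at a follow-up visit.

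The Study timeline section gives the arms different starting points: the baseline assessment for control, and the consultation meeting for both intervention groups. Of the consultation it says: "This will take place within 2 weeks after the baseline assessment since the personalised advice needs to be composed by the nutritionist". The article gives no visit window, no expected event rate for these outcomes, and no statement of which date the 3- and 6-month visits are counted from when they are booked.

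**The concern.** True onset lies somewhere between two visits, but the model receives a calendar date as if onset had been observed on that day. Cox regression uses only the order of the times and who is still at risk at each one. Around 6 months, events and censorings fall within the same few weeks, because nearly everyone leaves the risk set at their own final visit. If one arm is seen slightly later on the analysis clock, its events are compared with a risk set from which much of the other arm has already been censored. Its hazard then looks lower although the proportion affected is the same.

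This matters here because the arm-specific starting points can create such a difference. Depending on how visits are booked, two secondary outcomes could show a spurious benefit or a spurious harm.

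**Working it through.** **Inputs from the article.** Cox model, visit date as event time, two follow-up visits (taken as days 91 and 182), 1:1:1 allocation with 88 per group, 15% drop-out, and up to 14 days between baseline and consultation. The article gives no hazard ratio or event count for these analyses, so there is no planned figure to reproduce.

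**Assumptions, because the article gives no values.** Six-month risk about 10% (range 6-35% examined); visit dates normally distributed around the target day with SD 5-10 days (range 1-14 examined); lag from baseline to consultation uniform over 3-14 days; no true effect; 15% without a 6-month visit.

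**Step 1: the mechanism by hand.** Suppose a fixed share of those attending on a given day are found to have the event. Within the 6-month cluster, an arm's apparent hazard on day t is then proportional to f(t)/S(t). Here f is the density of visit dates and S the share of the arm not yet seen. Take two arms 7 days apart and the day midway between their means. The two densities are equal there, so the apparent HR (later versus earlier arm) is

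HR = [1 − Φ(3.5/SD)] / Φ(3.5/SD).

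At 3 months the risk set is not drained, because event-free participants stay in it, so the HR there is about 1. If half the events fall at each visit, the overall HR is roughly the square root of the 6-month value:

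| SD (days) | 6-month HR | Overall HR, approx. |
|---|---|---|
| 5 | 0.242/0.758 = 0.32 | 0.57 |
| 7 | 0.309/0.691 = 0.45 | 0.67 |
| 10 | 0.363/0.637 = 0.57 | 0.76 |

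**Step 2: simulation of a generic 7-day shift.** Latent onset is the same in both arms, status is seen only at visits, and Cox is fitted to visit dates, with 88 per arm and 10% risk:

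| SD (days) | Median HR | Type I error |
|---|---|---|
| 5 | 0.61 | 15% |
| 7 | 0.68 | 12% |
| 10 | 0.76 | 8% |

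With no shift and SD 7, the HR is 1.01 and type I error 3%. In large samples the 7-day HR runs from about 0.4 to 0.9 as SD goes from 1 to 14 days, and it hardly changes with event rate or tie method. Type I error rises with event rate: at SD 7 it is 12%, 17% and 28% for six-month risks of 10%, 20% and 35%.

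**Step 3: the booking arrangements the article leaves open** (lag 3-14 days, SD 5-10 days, 10% risk):

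| Visits booked from | Clock starts at | HR under no effect |
|---|---|---|
| each arm's own start | each arm's own start | about 1.0 (1.02-1.07) |
| baseline, all arms | each arm's own start | about 1.4-1.8 |
| consultation (intervention) | baseline or randomisation, all arms | about 0.55-0.75 |
| baseline, all arms | baseline, all arms | about 1.0 (0.99-1.02) |

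Type I error is about 3-6% in the first and last rows, and roughly 9-18% in the two middle rows.

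**Step 4: the alternative.** Complementary log-log regression by scheduled visit, on data with a 7-day shift and 88 per arm, gives HR 1.02-1.08 and type I error 3-5%. What remains above 1 is mostly the extra week at risk in the later arm. At a 14-day shift the HR reaches about 1.1.

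**The case against.** The strongest reply is that the bias needs the arms to differ in visit timing, and the article states no such difference. It defines one starting point per arm and starts the Cox clock from that same point. The natural, though not explicit, reading is that follow-up visits are counted from there too, and the HR is then about 1.0. Booking rules and visit windows are details that a journal article commonly leaves to the full protocol, so their absence is not a fault. All of this stands.

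A reader might infer from the 7-day figures that the planned analysis is biased towards the intervention by a known amount. The article does not support that. The 7 days and the SD are assumptions, and booking from baseline would push the HR the other way. Nor do the figures show that a common time origin is harmful. It creates a shift only if intervention visits are booked from the consultation. If they are booked from baseline, it removes one.

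The reply also points out that leaving Cox is not essential: Cox fitted to scheduled visit number instead of date gave HR 1.01-1.06 and type I error 2-5% in the 7-day case. That is correct, and it is a grouped-time analysis too. The choice of visit date as the time scale is what causes the trouble, and the article fixes that choice explicitly.

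Finally, the Discussion already warns that six months may yield too few incident cases, including for risk of sarcopenia. Few events limit how often a false positive would arise, but they do not remove the shift in the HR.

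**Conclusion.** The point holds as a sensitivity in a stated method. It is not a demonstrated bias. Using the visit date as an exact event time makes the HR for incident sarcopenia risk and mobility limitations depend on the visit calendar, and the arm-specific starting points make an arm difference possible. Under no effect, and on the assumptions above, the HR is about 1.0 in the benign booking arrangement. It is about 1.4-1.8 or 0.55-0.75 in the two others, with type I error of roughly 9-18%. The direction cannot be told from the article. The sizes rest on an assumed SD of 5-10 days, about 10% risk and a lag of 3-14 days. Two secondary outcomes are affected, and the primary outcome and the sample size are untouched. The change is worth making because it costs almost nothing and protects these analyses whichever date the visits were booked from.

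**What to change.** For these two outcomes, replace Cox regression on visit dates with a grouped-time analysis. Use one record per participant per scheduled visit (3-month, 6-month) up to the first event or last attended visit, and complementary log-log regression with visit as a factor, study arm and the planned covariates. The arm coefficient remains a log hazard ratio. A logistic link would give odds ratios, so reporting would then have to change. State in the same place which date the follow-up visits are booked from in each arm.

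The cost is a change of analysis wording, with no new data and no effect on the conduct of the trial. There are two downsides. A small time-at-risk effect remains if one arm really is seen later (HR about 1.02-1.1), and information in the exact visit date within an interval is not used.

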### Randomisation, allocation and masking

Randomisation by means of a stratified block randomisation procedure will be performed by an independent statistician. Participants will be allocated in a 1:1:1 ratio to the three groups. The size of the randomisation blocks is three. Participants will be stratified according to their baseline habitual protein intake (<0.9 or 0.9–1.0 g/kg aBW/day) and sex to ensure homogeneous distribution of baseline habitual protein intake and sex in the three groups across the two recruitment sites, because there may be a different intervention effect by baseline habitual protein or sex. In case couples are eligible, we will allocate them to the same intervention group to limit interference between intervention groups. We will randomly select on which partner the randomisation for the intervention group is based. Any resulting unbalance in the number of subjects per treatment arm will be corrected in the randomisation of the next block. Due to the nature of the study, researchers, nutritionists and participants are not blinded to the study group.

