### Sample size and statistical analyses

#### Sample size

The study is powered to detect a substantial meaningful change of 28 s (SD=61 s)^69^ between the respective intervention groups and the control group on the primary outcome walk time on the 400 m walk test, assuming a two-sided test at α=0.05 with a power of 0.8. For this, 75 participants per group are needed, which is 225 in total. Assuming a drop-out of 15% (which was reported in a comparable study of Bhasin *et al*,^19^ the total number of study participants to be included in the study is n=264. Therefore, we aim to include a total of n=132 at each study site (n=44 per study group per study site).

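### Subgroup effects are to be analysed stratum by stratum with no interaction test named, although the stated interest is whether the effect differs between strata

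*Protocol article*

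**What the plan says.** The Statistical analyses plan section of the protocol article fixes the factors, the cut-points and the method, and applies them to primary and secondary outcomes alike: "We will perform subgroup analyses stratified by baseline protein intake (<0.9 or 0.9–1.0 g/kg aBW/day), sex and baseline 400 m time (based on median"). Each intervention group is compared with control, and the mixed model adjusts for baseline walk time, baseline protein intake and sex. The only decision rule given is a two-sided p value of 0.05, with no separate rule for subgroups. No interaction term or test appears anywhere in the article.

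The section on randomisation stratifies by protein intake and sex. One reason is even distribution across the groups. The other is "because there may be a different intervention effect by baseline habitual protein or sex".

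The Sample size section covers the whole-group comparison only: "The study is powered to detect a substantial meaningful change of 28 s (SD=61 s"), "assuming a two-sided test at α=0.05 with a power of 0.8". The result is "For this, 75 participants per group are needed, which is 225 in total".

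**The concern.** Whether the advice works differently at lower and higher protein intake, or in men and women, is a question about the difference between two effects. Fitting the model separately in each stratum gives two estimates and two p values. Neither p value tests that difference. A stratum with about half the participants has much less power than the whole trial, so an effect that is the same everywhere can easily reach p < 0.05 in one stratum and miss it in the other.

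What is at stake is how the subgroup results are read. The Discussion says the trial will inform whether the recommended protein intake for older adults should be raised. A chance pattern that looks like benefit only below 0.9 g/kg aBW/day would bear on that question. The primary whole-group analysis is not affected.

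**Working it through.** **Inputs from the article.** Difference 28 s, SD 61 s, two-sided α = 0.05, power 0.80, 75 evaluable per group, 1:1:1 allocation, and three two-level subgroup factors. The walk-time factor is a median split, so close to 50:50. The article gives no expected split for protein intake or sex, so other splits below are assumptions.

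**1. The plan's own figure.** n = 2(1.960 + 0.842)² × 61² / 28² = 74.5, so 75 per group, as stated. The SE of the difference is 61 × √(2/75) = 9.96 s, and power is Φ(28/9.96 − 1.96) = 0.80. With 15% drop-out, 225/0.85 = 264.7, which agrees with the stated 264 within rounding.

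**2. Power in one stratum, even split (37.5 per arm).** SE = 61 × √(2/37.5) = 14.1 s. Power = Φ(28/14.1 − 1.96) = 0.511.

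**3. Chance that exactly one of two strata is significant when the effect is the same in both.** The strata contain different people, so P = p₁(1 − p₂) + p₂(1 − p₁). For an even split this is 2 × 0.511 × 0.489 = 0.50. Both strata are significant in 26% and neither in 24%. A simulation of 40,000 trials with two contrasts sharing one control group also gave 0.50 for each factor and contrast.

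**4. How far this depends on the assumptions.**

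| Change from the base case (28 s, SD 61 s, 75 per group, 50:50) | Exactly one stratum significant |
|---|---|
| None | 50% |
| Split 30:70 (powers 0.337 and 0.652) | 55% |
| Split 25:75 (powers 0.290 and 0.682) | 58% |
| All 88 per group analysed | 49% |
| True effect 14 s | 28% |
| True effect 42 s | 26% |
| No effect | 10% |
| Residual SD 50 s (assumed) | 44% |
| Residual SD 40 s (assumed) | 24% |
| Residual SD 30 s (assumed) | 4% |

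The residual SD matters because the model adjusts for baseline walk time, and the article does not say whether 61 s is the SD of walk time, of its change, or of a residual.

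**5. The interaction test.** It errs in 5% of trials per factor and contrast whenever the effect is uniform, whatever its size. For an even split its SE is 61 × √(4/37.5) = 19.9 s. Power for a 28 s difference between strata is Φ(28/19.9 − 1.96) = 0.29. For 80% power the difference would have to be 2.80 × 19.9 ≈ 56 s.

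**6. Multiplicity on the same footing.** On the primary outcome there are 3 factors × 2 levels × 2 contrasts = 12 stratum tests, or 3 × 2 = 6 interaction tests. In a simulation of 20,000 trials with no effect, three independent even factors and a shared control group, at least one was significant in about 35% for the 12 stratum tests and about 25% for the 6 interaction tests.

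**The case against.** The strongest objection is that the article is silent on an interaction test and does not rule one out. Stratum estimates often accompany such a test, the article is condensed, and a fuller analysis plan may exist. This stands in part: a reader might infer that the trial will not test interactions at all, and the text does not support that. But the article does not leave the subgroup method open. It names factors, cut-points, outcomes and a stratified method, and that method does not match the reason given in the randomisation section.

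Second, a reader might infer that a uniform effect will look subgroup-specific half the time whatever happens. That is too strong. For an even split 50% is the maximum over effect sizes, and the rate drops quickly with a smaller residual SD. It also assumes someone reads significance in one stratum only as a subgroup effect. The article plans no such claim, and subgroups appear in none of its stated objectives.

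Third, it is tempting to object to the cut-points themselves. The 0.9 g/kg cut is the randomisation stratum, and the median split uses a baseline variable without reference to outcome or allocation. Modelling these measures as continuous is largely a matter of preference.

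Fourth, interaction tests do not remove the multiplicity problem: about 25% familywise error on the primary outcome, against about 35%, is a modest gain. This stands, and it is why the results also need an exploratory label.

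**Conclusion.** The point holds as a mismatch between method and question. The article fixes stratified subgroup analyses, names no test of the difference between strata, and gives a possible difference in effect as a reason for its interest in two of the three factors.

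At the planning values, with a uniform 28 s effect and an even split, exactly one of two strata would be significant in about 50% of trials per factor and contrast, ten times the 5% of an interaction test. With a 14 s effect, or with an assumed residual SD of 40 s, it is still about five times. With no effect it is about twice. Only at a much smaller residual SD, such as 30 s, does the gap close. The mismatch does not depend on the exact percentage. The change should be made, but it concerns subgroup conclusions only.

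**What to change.** For each of the three factors, add a treatment-by-factor interaction to the full adjusted model, for each intervention group against control, and state that any claim of a subgroup difference will rest on that test alone. Show stratum estimates with 95% CIs as description. Label all subgroup results exploratory, especially those for secondary outcomes. Protein intake and walk time may be added as continuous modifiers in a supportive analysis, at the price of an assumption about functional form.

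This needs a few sentences and extra model terms, with no new data or participants. The plan should state three costs openly:

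- Interaction power is low, about 29% for a 28 s difference between strata, so a non-significant test is not evidence of equal effects.
- Interaction terms may be unstable for sparse binary and time-to-event outcomes; the Discussion itself warns that incident cases may be few.
- Six interaction tests on the primary outcome still carry about a 25% chance of at least one false positive when there is no effect.

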Participants in intervention group 2 will receive the same dietary advice as intervention group 1, and the personalised advice to consume at least 7.5–10 g protein through protein-(en)rich(ed) food products within half an hour after performing usual physical activity as this may enhance resistance exercise-induced MPS.^27^ One RCT among older adults has shown that protein supplementation in combination with resistance exercise had beneficial effects on, for example, muscle mass and function, but no differences in effect were found between protein consumption pre-resistance versus post-resistance exercise.^43^ We therefore recommend protein intake after physical activity as this is a uniform and more feasible advice compared with ‘in close proximity of’, and might also result in less stomach discomfort as compared with protein consumption prior to physical activity. Usual physical activity is defined as either physical exercise (eg, biking, swimming, tennis) or the most intensive activities of daily living when the participant does not engage in physical exercise (eg, gardening, housekeeping, doing groceries) for a minimum of 30 min. The advice is linked to most extensive or longest physical activity. Participants are instructed not to become more or less physically active but merely to shift their physical activity or protein intake moment.

During the intervention period, nutritionists will plan follow-up phone calls in consultation with the participants during week 2, week 4, week 8, week 16 and week 20 to ask if they have understood the advice and are able to adhere to the advice. In addition, any issues related to the use of protein-enriched food product can be discussed (intervention groups only). If necessary, changes in the dietary advice will be made, for example when weight change >2 kg has occurred (based on self-assessment). Participants allocated to the control group do not receive any intervention, but are contacted on similar time points as the intervention groups to ask how they are doing.

All participants are invited to a minimum of one organised lecture on non-health-related themes and other social events during the trial in order to stimulate their commitment to the trial. Separate lectures/events (with the same topic) are organised for the intervention groups and the control group to prevent interference between intervention arms. Participants can freely attend those lectures and all travel costs will be reimbursed.

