Per-protocol analyses will also be conducted as a sensitivity analysis. Effect estimates for change in primary and secondary outcome measures will be calculated for participants from the intervention groups who reached the protein target of at least 1.2 g/kg aBW/day after both 3 and after 6 months (mean protein intake based on the three 24-hour dietary recalls) versus participants from the control group. Data will be analysed using SPSS (IBM SPSS Statistics, Version 26). A two-sided p value of 0.05 is considered statistically significant.

The cost-effectiveness analysis will be performed from a healthcare perspective. Total mean costs during the study will be related to physical functioning (the 400 m walk test) and change in quality-adjusted life-years based on the EuroQol 5D Questionnaire. Mixed model regression analyses will be used to estimate differences in the primary outcome of the respective intervention groups versus the control group. Linear regression analyses will be used to estimate differences in QoL (expressed as quality-adjusted life-years) and healthcare costs. Incremental cost-effectiveness ratios will be calculated by dividing the difference in costs by the difference in effects. Statistical uncertainty will be estimated using bias-corrected accelerated bootstrapping (5000 replications) and will be presented using cost-effectiveness planes and cost-effectiveness acceptability curves.

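### The per-protocol analysis selects intervention participants on intake measured after randomisation and sets no criterion for controls, so it is a non-randomised comparison rather than a sensitivity check of the randomised effect

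*Protocol article*

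**What the plan says.** The Statistical analyses plan section of the protocol article makes intention-to-treat the primary analysis, whatever the adherence. The model is adjusted for baseline 400 m walk time, baseline protein intake and sex. The section then adds: "Per-protocol analyses will also be conducted as a sensitivity analysis". Effects on primary and secondary outcomes are to be estimated "for participants from the intervention groups who reached the protein target of at least 1.2 g/kg aBW/day after both 3 and after 6 months", with participants from the control group as comparator. No intake, adherence or attendance criterion is given for controls.

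The Intervention section gives group 2 one component more than group 1: advice to "consume at least 7.5–10 g protein through protein-(en)rich(ed) food products within half an hour after performing usual physical activity". The per-protocol definition does not mention it.

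**The concern.** The rule conditions on something that happens after randomisation, and does so on one side only. Whoever fails to reach the target is removed from the intervention groups, while the corresponding people stay in the control group. Any characteristic that affects both reaching the target and the change in walk time then separates the groups.

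The design offers a concrete route. The Study timeline places the 6-month dietary assessment one week before the final visit. A participant whose health declines during the trial may miss the target because of that decline and also walk more slowly. Adjusting for baseline covariates, even if carried over to this analysis, cannot remove confounding that arises after baseline.

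Two consequences follow. First, calling the result a sensitivity analysis suggests a check on the same randomised effect. If the intention-to-treat result were null, a favourable target-reacher estimate could be read as showing that protein works in those who adhere. Second, a group 2 participant who met the protein target but never followed the timing advice would count as per-protocol, although timing is what distinguishes that group from group 1.

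**Working it through.** **The plan's own figure.** The Sample size section states "The study is powered to detect a substantial meaningful change of 28 s (SD=61 s", "assuming a two-sided test at α=0.05 with a power of 0.8", and concludes that "75 participants per group are needed, which is 225 in total". Per group, n = 2 × (1.960 + 0.842)² × 61² / 28² = 74.5, so 75, and 3 × 75 = 225. With 15% drop-out, 225 / 0.85 = 264.7 against the stated 264, a rounding difference with no bearing here. The figures reproduce and supply the scale: SD 61 s and a design difference of 28 s.

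**Selection bias under no true effect.** Let p be the share of an intervention group that reaches the target at both visits, and r the correlation between the underlying tendency to reach it and walk-time improvement. The article gives neither, so both are assumptions. Treating the tendency as standard normal, with the top fraction p selected:

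- selection shift = φ(z) / p, where z cuts off the upper fraction p;
- spurious difference = r × shift × SD, with the unadjusted SD of 61 s.

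For example, with p = 0.5 the shift is 0.399 / 0.5 = 0.798, and r = 0.2 gives 0.2 × 0.798 × 61 = 9.7 s.

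The table gives the spurious difference. In brackets is the two-sided 5% test's false-positive rate for one intervention group versus control, with 75 control completers, 75p selected participants and no covariate adjustment.

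| p | Shift | r = 0.1 | r = 0.2 | r = 0.3 |
|---|---|---|---|---|
| 30% | 1.159 | 7.1 s (7.7%) | 14.1 s (16.4%) | 21.2 s (31.8%) |
| 50% | 0.798 | 4.9 s (6.8%) | 9.7 s (12.7%) | 14.6 s (23.0%) |
| 70% | 0.497 | 3.0 s (5.9%) | 6.1 s (8.6%) | 9.1 s (13.4%) |

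Against 28 s, the range runs from 3.0 / 28 = 11% to 21.2 / 28 = 76%.

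**Effect of baseline adjustment.** If the primary-model covariates are carried over and r is read as a residual correlation, it should multiply the residual SD. Suppose, as a further assumption, that the covariates explain half the variance. The residual SD is then 61 × √0.5 = 43 s and every difference falls by about 29%, giving roughly 2 to 15 s. With r = 0 there is no bias at any p.

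**The case against.** The strongest reply is that the article already keeps this analysis in its place. Intention-to-treat is primary, the selection rule is disclosed, and nothing lets the per-protocol result override a null primary result. That is right and limits the severity, but it does not make the comparison randomised or the label accurate.

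A reader might infer that the analysis is shown to favour the intervention. The documents do not support that. They do not describe target-reachers as healthier or more motivated. The advice is meant to leave total energy intake unchanged and the enriched products are free, so appetite need not be the driver. Attainment also rests on at most three recalls per time point, and measurement noise would weaken any link with health. The direction is a plausible inference and the size depends on assumed values.

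A reader might also infer that two-stage least squares with the 1.2 g/kg threshold as a binary exposure would settle the matter. It would not. It assumes that allocation has no effect in those who miss the target, yet someone moving from, say, 0.85 to 1.15 g/kg aBW/day would count as untreated and might still benefit. The complier estimate would then be inflated.

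On group 2, it can be said that the article openly defines the set by protein intake and that a finer definition may sit in a fuller plan. The definition is nevertheless stated, and the name claims more than it covers. Correcting the name needs no new measurement.

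**Conclusion.** The point holds as a statement about what the analysis is. One-sided selection on post-randomisation intake makes it a non-randomised comparison, and this follows from the stated rule rather than from missing detail. Bias towards the intervention is plausible but not demonstrated. The 3–21 s (11–76% of 28 s) is an illustration that rests on assumed attainment of 30–70%, an assumed correlation of 0.1–0.3 and the unadjusted SD. It is not an estimate of the bias this trial will have. The primary analysis is not compromised. The change is worthwhile because it is cheap and because the present label invites a causal reading that the comparison cannot carry.

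**What to change.** Keep intention-to-treat as primary, and then:

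1. **Group 1 versus control.** Make the adherence analysis an instrumental-variable analysis (two-stage least squares) in all participants randomised to these two groups. Use allocation as instrument, mean protein intake at 3 and 6 months (g/kg aBW/day) as a continuous exposure, and the primary-model covariates. State the exclusion restriction, namely that allocation affects walk time only through mean intake. Note where it may be strained, for instance by the advice to take one daily meal with at least 35 g protein.
2. **Target-reacher comparison, if kept.** Label it a non-randomised, exploratory comparison of protein-target reachers with controls, not a sensitivity check of the randomised effect.
3. **Group 2.** Call the set protein-target reachers rather than per-protocol, because the definition does not cover adherence to the timing advice.

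The cost is revised wording and one further model. The dietary recalls are already scheduled at both follow-up visits. The price is a wider confidence interval and an assumption that must be stated and defended.
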